#### 2.1.2. Inclusion and Exclusion Criteria

ASD Group: A total of 30 children diagnosed with ASD according to DSM-5 criteria (28 males, 2 females; age range: 9–14) will be recruited from Guangzhou Kangna School. Participants met the DSM-5 diagnostic criteria for ASD [1]. The Chinese version of the Gilliam Autism Rating Scale, Second Edition (GARS-2) [68] will be used, which includes three subscales: Stereotyped Behaviors, Communication, and Social Interaction. Scoring is based on DSM-IV-TR [69] and standards from the Autism Society of America (1994). The GARS-2 has shown good validity within the Chinese ASD population [70]. Non-verbal intelligence was assessed using the standard version of the Raven Progressive Matrices, and the scores were within the normal range (percentile ≥ 25).

TD Group: A total of 30 children with no history of neurological or psychiatric disorders (28 males, 2 females; age range: 9–14) will be recruited from Guangzhou Yongxing Primary School. The TD group and ASD group are matched for gender ratio (male: female = 28:2), age (no significant difference between groups as determined by independent samples t-test), and non-verbal intelligence (Raven test scores matched). All participants are native speakers of Mandarin Chinese and right-handed.

Participants will be excluded if they have any of the following conditions: uncorrected hearing impairment, a history of epilepsy or other neurological disorders, hearing abnormalities as indicated by a pure-tone audiometry threshold greater than 25 dB HL, or an inability to cooperate with the experimental tasks, such as excessive head movement or a gaze rate below 70%.

### 2.2. Stimuli, Experimental Procedure and Measurements

#### 2.2.1. Auditory Stimuli and Phonological Manipulations

The auditory stimuli consist of eight standardized Mandarin monosyllabic words: /da1/ (level tone), /da4/ (falling tone), /du1/ (level tone), /ba1/ (level tone), /du4/ (falling tone), /ba4/ (falling tone), /bu1/ (level tone), /bu4/ (falling tone). The design systematically manipulates three phonological dimensions: tone (level1 vs. Falling4), vowel (/a/ vs. /u/), and consonants (/d/ vs. /b/). The prepared stimuli were recorded in a soundproof chamber by a native Mandarin-speaking male announcer, using Neundo 4 software (version 4.3.0, Steinberg Media Technologies, Hamburg, Germany) with a sampling rate of 44.1 kHz and a 16-bit resolution in mono. A male speaker was chosen to facilitate consistent F0 control and reduce pitch-related variability across stimuli. Acoustic parameters were standardized using Praat software(version 5.3.51, University of Amsterdam, Amsterdam, The Netherlands) [71]. While duration, intensity, and fundamental frequency are explicitly controlled, other acoustic properties such as voice quality, spectral tilt, and formant trajectories are not formally quantified. The fundamental frequency (F0) setup is as follows: level tone (M = 170 Hz) and falling tone (M = 178 Hz) (see Figure 1a). The duration of each stimulus is fixed at 300 ms, and the sound intensity is normalized to 70 dB SPL. Although we do not formally evaluate additional acoustic parameters such as amplitude envelope, spectral tilt, or formant trajectories, all recordings were produced by the same native Mandarin-speaking male speaker under consistent recording conditions using a clear, child-directed register to minimize within-category variability. The standard stimulus /ba1/ is chosen for its acoustic stability and developmental appropriateness. As a familiar and emotionally neutral syllable with a level tone and simple CV structure, it provides a clear perceptual baseline for detecting phonological deviations.

As this study focuses exclusively on phonological processing of speech sounds, the semantic content of the syllables is not emphasized or manipulated. Each stimulus is a real Mandarin monosyllable with multiple potential lexical meanings, but none are presented with semantic or contextual cues. To minimize potential lexical confounds, all stimuli are selected to be phonotactically legal, emotionally neutral, and matched in syllable structure and duration. Word frequency is not used as an experimental factor, as each syllable in the stimuli is associated with multiple Mandarin homophone candidates. Although all stimuli are phonotactically legal real Mandarin monosyllables, no semantic context is provided, and the task design (passive listening) minimizes lexical access.

The selection of tones, vowels, and consonants is guided by both phonetic salience and linguistic relevance. We use Tone 1 (high-level) as the standard due to its acoustic stability and neutral contour, providing a perceptually robust baseline. Stimuli with Tone 4 (falling) are chosen as deviants for their clear contrast in pitch trajectory, which facilitates reliable MMN detection. The vowel contrast between /a/ and /u/ is selected to capture differences in tongue position and rounding while controlling for stimulus duration and syllable structure. For consonants, /b/ and /d/ differ in place of articulation but share similar voicing, allowing us to examine segmental contrasts while minimizing voicing confounds.

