#### 2.3.4. Representational Similarity Analysis

Representational Similarity Analysis (RSA) has been effectively applied in prior studies to decode different linguistic feature representations, such as decoding multidimensional phonological representations and feature integration in language processing [77,78,79]. To investigate how different speech features (tone, vowel, consonant) are neurally represented and whether individuals with ASD exhibit altered feature integration, we perform RSA based on ERP data. Integration Complexity Models are constructed to quantify the dissimilarity stimuli (see Figure 3). Each model operationalizes dissimilarity between stimulus pairs as a function of changes in three phonological features: Tone, Vowel, and Consonant. The models differ in their weighting schemes to emphasize specific features, reflecting theoretical assumptions about their relative perceptual or cognitive salience. Below is a detailed description of each model:

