##### Step 1: Constructing Theoretical RDM Models

Base Feature-Count Model

This baseline model assumes equal perceptual salience across all three features. Dissimilarity between two stimuli is defined as the sum of the number of altered features. Specifically: Tone, Vowel, or Consonant change contributes a unit weight of 1. For example, a stimulus pair differing in both Tone and Vowel (e.g., /da1/ vs. /du4/) receives a dissimilarity value of 2, while a pair differing in all three features (e.g., /da1/ vs. /bu4/) results in a value of 3. This additive framework generated a symmetric 8 × 8 RDM, with diagonal values (self-comparisons) set to 0 and off-diagonal values ranging from 1 to 3.

Tone-Weighted Model

To test the hypothesis that Tone carries higher perceptual salience in speech processing, this model assigns a doubled weight (2) to Tone changes, while maintaining unit weights (1) for Vowel and Consonant changes. Dissimilarity values are calculated as follows: A Tone change alone (e.g., /da1/ vs. /da4/) contributes a dissimilarity of 2. A combination of Tone with another feature (e.g., Tone + Vowel: /da1/ vs. /du4/) results in a summed value (2 + 1 = 3). Full feature changes (Tone + Vowel + Consonant) yield a maximum dissimilarity of 4 (2 + 1 + 1). This model’s RDM retains symmetry but amplifies dissimilarities involving Tone changes compared to the base model.

Vowel-Weighted Model

This model prioritizes Vowel changes with a weight of 2, hypothesizing that vowel identity dominates perceptual discrimination. Tone and Consonant changes retain unit weights (1). Key calculations included: A Vowel-only difference (e.g., /da1/ vs. /di1/) produces a dissimilarity of 2. Combinations involving Vowel changes (e.g., Vowel + Consonant: /da1/ vs. /bu1/) generate higher values (2 + 1 = 3). Triadic feature changes (Tone + Vowel + Consonant) reach a dissimilarity of 4 (1 + 2 + 1). The RDM structure emphasizes vowel-related distinctions while preserving additive feature contributions.

Consonant-Weighted Model

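### Within a group, the ranking of the tone-, vowel- and consonant-weighted RDMs cannot separate feature salience from acoustic size, because no acoustic distance common to the three contrasts is measured

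*Protocol article*

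**What the plan says.** **Stimuli (Section 2.2.1).** Eight recorded syllables cross two consonants, two vowels and two tones. On acoustics, the section says: "While duration, intensity, and fundamental frequency are explicitly controlled", "other acoustic properties such as voice quality, spectral tilt, and formant trajectories are not formally quantified". It repeats the point later: "we do not formally evaluate additional acoustic parameters such as amplitude envelope, spectral tilt, or formant trajectories". On duration it says: "The duration of each stimulus is fixed at 300 ms". Intensity is normalised, and mean F0 is given as 170 Hz for the level tone and 178 Hz for the falling tone. The text does not state the size of the fall.

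**Models (Section 2.3.4, Step 1).** The base RDM counts changed features, with "off-diagonal values ranging from 1 to 3". Three further RDMs double the weight of tone, vowel or consonant. The weights are described as "reflecting theoretical assumptions about their relative perceptual or cognitive salience"; the vowel version is introduced as "hypothesizing that vowel identity dominates perceptual discrimination".

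**Use (Step 3).** Each neural RDM is compared with each model RDM by Spearman correlation, separately for the two groups. The weighted models are said to express differential salience of the three cues.

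**The concern.** The article's own introduction (Sections 1.1.2 and 1.1.3) says that vowels are told apart mainly by their formants, and consonants by formant transitions, bursts and spectral properties. Several of these carriers are what Section 2.2.1 leaves unquantified. The same section picks the falling tone because its clear pitch contrast helps MMN detection, so the plan accepts that physical contrast size affects the response.

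A purely acoustic account is therefore a natural rival to the salience account, yet no specified model represents it. If, say, the Vowel-Weighted RDM fits best in a group, the finding would be reported as the salience of vowels. It could equally mean that this speaker's /a/ and /u/ differ more, physically, than his /b/ and /d/ or his two tones.

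**Working it through.** **Inputs.** Stimuli from Table 3; weights from Section 2.3.4, Step 1. The acoustic distances are assumptions, because the article gives none.

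**Rebuilding the plan's RDMs.** Eight stimuli give 8 × 7 / 2 = 28 pairs. There are seven possible change patterns, each occurring in 4 pairs. The base model then has 12 pairs at 1, 12 at 2 and 4 at 3, which reproduces the stated range of 1 to 3. Each weighted model has 8, 8, 8 and 4 pairs at 1, 2, 3 and 4, which reproduces the stated maximum of 4.

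**An acoustic RDM with no salience term.** Add assumed distances for tone/vowel/consonant of 1/1.25/1. The table shows mid-ranks as deviations from their mean of 14.5, with 4 pairs per row.

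| Change | Base | Vowel-weighted | Tone-weighted | Acoustic 1/1.25/1 |
|---|---|---|---|---|
| T | −8 | −10 | −2 | −10 |
| V | −8 | −2 | −10 | −4 |
| C | −8 | −10 | −10 | −10 |
| T+V | +4 | +6 | +6 | +6 |
| T+C | +4 | −2 | +6 | 0 |
| V+C | +4 | +6 | −2 | +6 |
| T+V+C | +12 | +12 | +12 | +12 |

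Sums of squares: base 4 × 384 = 1536; each weighted model 4 × 424 = 1696; acoustic 4 × 432 = 1728. Spearman's rho is the sum of cross-products divided by the square root of the product of the two sums of squares.

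- Acoustic with Vowel-Weighted: 1696 / √(1728 × 1696) = 0.991
- Acoustic with base: 1536 / √(1728 × 1536) = 0.943
- Acoustic with Tone-Weighted: 1312 / √(1728 × 1696) = 0.766 (Consonant-Weighted is the same by symmetry)
- Base with any weighted model: 1440 / √(1536 × 1696) = 0.892
- One weighted model with another: 1184 / 1696 = 0.698

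**Other assumed ratios (additive).**

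| Tone/vowel/consonant | Base | Tone-W | Vowel-W | Consonant-W |
|---|---|---|---|---|
| 1/1/1 | 1.000 | 0.892 | 0.892 | 0.892 |
| 1/1.25/1 | 0.943 | 0.766 | 0.991 | 0.766 |
| 1/2/1 | 0.892 | 0.698 | 1.000 | 0.698 |
| 1/3/1 | 0.825 | 0.617 | 0.991 | 0.617 |
| 2/1/1 | 0.892 | 1.000 | 0.698 | 0.698 |
| 1/1/2 | 0.892 | 0.698 | 0.698 | 1.000 |

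Among these, only equal distances return the base model. Combining distances by a Euclidean rule instead of addition leaves the same winner in every row.

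**Two groups.** Both groups were given the same acoustic RDM (1/2/1) plus random noise, with 3,000 simulated RDMs each. With equal noise, the mean difference in fit was within ±0.003 for all four models. With noise SD 1 against 2, the vowel-weighted fit fell from 0.73 to 0.46, but the base fit fell too, from 0.65 to 0.41. That is lower reliability, not altered weighting.

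**Can partialling separate the two?** With n the neural RDM, m a model and a the acoustic RDM, the partial correlation is (r_nm − r_na·r_am) / √[(1 − r_na²)(1 − r_am²)]. If the fit to m runs only through a, then r_nm is about r_na·r_am and the partial is about 0, as wanted. If a and m are rank-identical, as at 1/2/1, then r_am = 1 and r_nm = r_na, so the expression is 0/0. At 2/3/1 the acoustic RDM correlates 0.982 with the Vowel-Weighted RDM, leaving 1 − 0.982² ≈ 4% of the rank variance unshared.

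**The case against.** **The models may be meant acoustically.** Step 3 defends additivity by saying that early encoding follows separable acoustic dimensions, and the weights are called perceptual as well as cognitive. A larger contrast being more perceptible contradicts nothing. This has force for a claim about these particular recordings. It does not carry over to a claim about tone, vowel or consonant as a feature, nor to cognitive salience, nor to the study's declared focus on phonological processing.

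**The group comparison.** A reader might infer that an ASD–TD difference in fit would be an acoustic artefact. The documents do not support that: both groups hear the same files, and a uniform gain leaves Spearman fit unchanged. The RSA predictions P4–P6 and P10–P12 are group contrasts, and none names the tone-, vowel- or consonant-weighted model. The calculation also says nothing about the Integrated Features, Segmental-Only or Complexity-Weighted models in P5, P6 and P11. These objections stand and set the limits of the point.

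**Acoustics are not wholly ignored.** Duration and intensity are equalised, F0 is controlled with its means reported, and Figure 1a is described as showing spectrograms and pitch contours. This stands. What is lacking is a distance on one scale for all three contrasts.

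**Disclosure.** The missing measurements are stated twice. Section 6 concedes that the RDMs may oversimplify acoustic–phonetic reality, and calls the study exploratory. But it treats this as a matter of ecological validity and never says that a weighted fit could be acoustic.

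**Conclusion.** The point holds for the within-group ranking of the weighted models. With the plan as written, a win for one of them cannot be attributed to salience rather than acoustic size: an assumed excess of 25% in one contrast is enough to make its weighted model fit best (0.991 against 0.943 for base). The candidate models also overlap heavily (0.892 and 0.698), so there is little room to tell them apart.

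The result rests on assumed distance ratios and on distances that combine additively or by a Euclidean rule. That the three contrasts really are unequal in physical size is not shown; the article reports neither matching nor mismatch. For group differences the consequence is one of interpretation only: a difference in weighted-model fit could not be assigned to phonological rather than acoustic coding. Data collection, the univariate ERP comparisons and the integration models are not called into question here.

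**What to change.** Before the RSA is interpreted:

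1. Compute an 8 × 8 acoustic RDM from the existing recordings, using time-aligned spectral distance and F0-contour distance. Show the two parts separately as well as combined, because their relative weighting is itself a choice.
2. Report its Spearman correlation with each of the four model RDMs.
3. Enter it as a competing model in Step 3.
4. Use partial Spearman correlations controlling for it only where the acoustic and model RDMs are not nearly collinear. Where they are, state that acoustic size and salience cannot be separated for that feature, and make no salience claim.
5. State in the article that a group difference in weighted-model fit does not by itself show altered phonological weighting.

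The cost is a few hours of analysis on files already recorded, with Praat already in use, and no new participants or EEG. The price is a smaller unique fit for each phonological model and, for some features, possibly no separable conclusion about salience.

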#### 2.2.2. Oddball Paradigm and Experimental Procedure

The experiment adopts a multi-feature oddball paradigm with /ba1/ as the standard stimulus, which appears in 50% of the trials (980 instances). The remaining 50% of the trials (980 instances) consist of seven types of deviant stimuli, each comprising 7.14% of the total. The deviant types include single-feature changes (e.g., from /ba1/ to /ba4/, a change in flat tone to falling tone) and combined-feature changes (e.g., from /da1/ to /bu4/, which has consonant + vowel + tone changes). The full set of stimuli is summarized in Table 3 below:

Stimulus presentation is controlled using the E-Prime 2.0 software. Auditory stimuli are delivered binaurally via a Presonus Firebox audio interface and KOSS PORTA PRO headphones, with the sound intensity calibrated to 65 dB SPL. Each stimulus has a duration of 300 ms, and the stimuli are presented with a randomized stimulus onset asynchrony (SOA) ranging from 950 to 1050 ms, corresponding to an interstimulus interval (ISI) of 650 to 750 ms. The entire experimental session lasts approximately 35 min. To allow participants to adapt to the auditory environment, 20 standard stimuli are presented prior to data collection; these are be excluded from the formal analysis. Participants are instructed to passively listen to the stimuli while watching a self-chosen silent animation throughout the experiment to maintain visual engagement and minimize movement artifacts (see Figure 1a,b).

### 2.3. Data Analysis

#### 2.3.1. EEG Data Acquisition and Preprocessing

Continuous EEG data will be acquired using a 32-channel Brain Products system (10–20 montage) referenced to the left mastoid, with a ground electrode at AFz. Horizontal and vertical electrooculograms (HEOG/VEOG) are additionally used to monitor ocular artifacts. Data are sampled at 1000 Hz with a 0.016–250 Hz bandwidth and impedance maintained below 10 kΩ.

Offline processing in EEGLAB 14.1.0 includes downsampling to 250 Hz, PREP pipeline noise removal [72], 1–30 Hz bandpass filtering, and artifact rejection (±75 µV threshold). Independent component analysis (Fast ICA) will be implemented to remove ocular artifacts, with data re-referenced to the average of all electrodes.

#### 2.3.2. ERP Epoching and Feature Extraction

For each trial, EEG data are segmented into epochs ranging from 100 ms before to 700 ms after stimulus onset. Baseline correction is applied using the pre-stimulus interval (−100 to 0 ms). ERP waveforms are averaged separately for each condition, and the resulting averages are used in subsequent statistical analyses and group comparisons.

#### 2.3.3. Temporal Principal Component Analysis

Given the use of a multi-feature oddball paradigm in the present study, the ERP components elicited by different deviant types are likely to overlap temporally, making it challenging to isolate the MMN using conventional fixed-window analysis. Prior studies have successfully applied temporal principal component analysis (t-PCA) to decompose overlapping ERP components and better isolate specific responses such as the MMN in oddball paradigms [73,74]. To address this issue, this study will employ t-PCA, a data-driven approach to decompose the ERP signal into latent temporal components. t-PCA enables the extraction of principal components that account for the majority of variance in the time domain, and through rotation and back-projection, allows psychologically meaningful components to be reconstructed in ERP space [75]. Compared to traditional averaging methods, t-PCA offers improved component separation, higher signal-to-noise ratio, and greater sensitivity in detecting condition-specific effects—advantages particularly critical for paradigms involving multi-dimensional speech feature processing (see Figure 2).

To extract multiple ERP components elicited by the multi-feature oddball paradigm, including early mismatch negativity (eMMN), and late mismatch negativity (lMMN), we decompose the time-domain covariance structure of the ERP data and identifies latent temporal components that account for the greatest proportion of variance in the signal.

t-PCA is applied across all conditions and participants, using the covariance matrix and Promax oblique rotation to enhance interpretability and allow for potential correlations among components. Component selection was guided by three criteria: (1) latency and temporal distribution of the component; (2) polarity and waveform characteristics; and (3) topographic distribution across the scalp. Based on previous literature and the typical temporal-spatial profiles of the target components, the following components are identified:eMMN: Early mismatch negativity (~100–200 ms; Fz, FCz, Cz)lMMN: Late mismatch negativity (~200–300 ms; Fz, FCz, Cz)P3a: Fronto-central positivity (~250–350 ms; Fz, FCz, Cz)

Once identified, components are back-projected into ERP space by multiplying temporal loadings with corresponding factor scores for each condition and participant. This is achieved by multiplying the component loadings with the corresponding factor scores for each condition and participant and reprojecting the resulting signal onto the original time axis. The reconstructed waveforms retain the component-specific variance structure while being interpretable in microvolt (µV) units, to facilitate traditional ERP analysis. For each reconstructed component (eMMN, lMMN, and P3a), mean amplitudes are calculated over representative electrode sites within the corresponding time windows. These values are then used in statistical analyses to assess condition effects and group differences in auditory feature processing. Importantly, we selected t-PCA because it enhances sensitivity to subtle neural effects by disentangling overlapping ERP components, isolating latent temporal patterns that may be masked in raw waveforms, and reducing noise through variance-based decomposition [76]. This is particularly critical in multi-feature paradigms, where temporal overlap between components (e.g., eMMN, lMMN, P3a) can obscure condition- and group-specific neural differences.

